### Plan for Access to the Full Protocol, Participant-Level Data, and Statistical Code

The protocol is available on the ClinicalTrials.gov website (NCT04375176). Study documents will be deidentified, stored by the Emergency and Trauma Research Centre, University of Insubria, and kept for at least 15 years in a locked secure office. All personnel involved in data analysis will be masked. Only the principal investigators and statisticians will have access to the final data set.

### Dissemination Plans

The results of the study will be released to participating physicians, referring physicians, and the medical community no later than 1 year after the completion of the trial, through presentations at scientific conferences and publications in peer-reviewed journals. Eligible authors will meet all 4 requirements of the ICMJE guidelines: (1) Substantial contributions to the conception or design of the work; or the acquisition, analysis, or interpretation of data for the work; (2) Drafting the work or revising it critically for important intellectual content; (3) Final approval of the version to be published; (4) Agreement to be accountable for all aspects of the work in ensuring that questions related to the accuracy or integrity of any part of the work are appropriately investigated and resolved.

### Ethics Approval

Protocol version 1.0 was approved by the Ethics Committee on April 16, 2020. The clinical trial will adhere to the principles of the Declaration of Helsinki and to the Clinical Trials Directive 2001/20/EC of the European Parliament on the approximation of the laws, regulations, and administrative provisions of the Member States relating to the implementation of Good Clinical Practices in the conduct of clinical trials on medicinal products for human use. All trial-related activities will be conducted with written informed consent and in accordance with relevant local and national guidelines.

## Results

 The study started on April 27, 2020. As of December 2020, we have enrolled 120 patients who have tested positive for SARS-CoV-2 and 30 healthy subjects. During January and February 2021, we enrolled 60 subjects from the health care workforce after they received the Pfizer vaccine.

The clinical data set is complete. Immunological analysis is ongoing, and we expect to complete this analysis by December 2022.

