Approximately 60 subjects (aged ≥18 years) from the health care workforce, for whom the date of the first administration of the Pfizer vaccine is already defined, will be studied at the following 3 time points: T0, prior to or on the day of the first administration of the vaccine; T1, between the 14th day after the first administration and the day of the second administration; and T2, between the 32nd and 35th days after the first administration.

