#### Additional Objective

We were also interested in characterizing the phenotypes and state of the degree of activation of peripheral blood mononuclear cells (PBMCs), including monocytes, NK cells, and CD4^+^ and CD8^+^ T cells, in healthy subjects vaccinated with the Pfizer vaccine.

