### Statistical Methods for the Primary and Secondary Outcomes

Associations between different variables will be examined using Pearson correlation coefficients. Paired comparisons will be made using the Wilcoxon matched pairs test. Nonpaired comparisons will be made using the 2-tailed Mann-Whitney test. Multiple comparisons will be made using appropriate one-way analysis of variance (ANOVA). A *P* value <.05 will be considered statistically significant. All statistical analyses will be performed using R version 3.4.3 (R Project for Statistical Computing) and SPSS 21 (SPSS Inc).

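### The article contradicts itself on whether the 60 vaccinees have a pre-dose baseline, and it allows a same-day T0 to be drawn after the injection

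*Protocol article*

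**What the plan says.** The extension is described at the end of Pathophysiological Considerations. It is to include roughly 60 adult health care workers, "for whom the date of the first administration of the Pfizer vaccine is already defined, will be studied at the following 3 time points". The baseline sample is defined as "T0, prior to or on the day of the first administration of the vaccine". The second sample falls between day 14 and the day of dose 2, and the third between days 32 and 35, both counted from dose 1.

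The same section gives the purpose: to learn what specific vaccination does to the immune cells. The Additional Objective is to characterise cell phenotypes and activation "in healthy subjects vaccinated with the Pfizer vaccine".

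The Results section, reporting on January and February 2021, states that "we enrolled 60 subjects from the health care workforce after they received the Pfizer vaccine".

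For analysis, Statistical Methods for the Primary and Secondary Outcomes says that "Paired comparisons will be made using the Wilcoxon matched pairs test". It names a suitable one-way ANOVA for multiple comparisons and sets one significance threshold of .05, with no adjustment mentioned.

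**The concern.** The plan describes people whose first dose is scheduled but not yet given. The Results section describes people who had already had it. Both are statements of fact in the current text, and they cannot both be literally true if T0 is to be a pre-dose baseline.

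What vaccination changes in monocytes, NK cells and T cells is a before-after question. Its only within-person reference is T0. The 30 healthy controls are different people and cannot stand in for it in a paired analysis. If some or all T0 samples were drawn after the injection, T1-T0 and T2-T0 are not changes from the unvaccinated state, and the article gives the reader no way to tell.

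A smaller issue is that two or three paired tests per marker, each at .05, carry a joint error rate above .05.

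**Working it through.** **1. Enrolment and T0 side by side.** The sentence in Results can be read in three ways:

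| Reading | T0 inside the stated window? | T0 before the injection? |
|---|---|---|
| Enrolled on a day after dose 1 | No | No |
| Enrolled on the day of dose 1, after the injection | Yes | No |
| Loose wording; actually enrolled before dose 1 | Yes | Yes, or same-day in unknown order |

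Only the third reading gives a usable baseline. No section says which applies or reports a count of T0 samples, so the number of true pre-dose baselines could be anything from 0 to 60.

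**2. Effect of a same-day, post-dose T0.** Let e be the shift already present when T0 is drawn, and d the true change from the pre-dose state to T1. The observed change is (d − e).

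- e in the same direction as d and smaller: the change is understated.
- e in the same direction as d and larger: the sign reverses.
- e in the opposite direction: the change is overstated.
- d = 0: a spurious change of −e appears.

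Pathophysiological Considerations says that innate cells act within minutes to hours and that a primary acquired response takes 4 to 8 days. So e should be near zero for T-cell markers on the vaccination day, but need not be for monocyte and NK markers. The direction is not fixed.

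**3. Error rate of the paired tests.** The article states no power, effect size or error rate for this cohort, so there is no figure of its own to reproduce.

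Inputs from the article: about 60 subjects, three time points, Wilcoxon matched pairs, threshold .05. Assumptions: normal data, exchangeable within-person correlation ρ from 0 to 0.9, no true change, 20,000 simulated trials per value of ρ.

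Reference values per marker:

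- two tests: 1 − 0.95² = 0.0975 if independent; upper bound 2 × 0.05 = 0.10;
- three tests: 1 − 0.95³ = 0.143 if independent; upper bound 3 × 0.05 = 0.15.

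Simulated chance of at least one false positive per marker:

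| ρ | T1-T0 and T2-T0 | All three pairs |
|---|---|---|
| 0 | 0.094 | 0.127 |
| 0.3 | 0.091 | 0.123 |
| 0.5 | 0.089 | 0.122 |
| 0.7 | 0.088 | 0.122 |
| 0.9 | 0.090 | 0.124 |

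The result hardly depends on ρ, for a simple reason. With unit variances, the covariance of the two differences from T0 is ρ − ρ − ρ + 1 = 1 − ρ, and each has variance 2(1 − ρ). Their correlation is therefore 1/2 whatever ρ is.

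Holm on the two contrasts compares the smaller P value with 0.05/2 = 0.025 and, if that passes, the larger with 0.05. This holds the error rate per marker at or below 0.05.

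**The case against.** The best defence is that the Results sentence is loosely written. The methods text describes staff with a dose date already set, and an author summarising recruitment of vaccinated staff could easily write that they were enrolled after vaccination. That may well be so. It is why the point is that the baseline is in doubt, not that it is absent. It does not remove the need for a correction, because two stated facts conflict and the T0 window alone does not ensure a pre-dose draw.

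A second defence is that this is an additional, descriptive objective, that the statistical section is headed for primary and secondary outcomes, and that a fuller protocol or analysis plan may handle multiplicity. This carries weight against the error-rate point, which is therefore secondary. It does not answer a contradiction inside the article.

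A reader might infer four stronger claims. The document does not support them:

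- **No suitable test is stated.** The Wilcoxon matched pairs test is stated and is valid for any two of the three time points.
- **Most of the power is lost through ANOVA.** An independent-groups ANOVA on T0, T1 and T2 would waste the pairing, but the article never assigns that form to these data. Its wording leaves room for the repeated-measures form, and the severity groups and controls are the natural place for the ordinary one.
- **A late T0 biases the effect toward zero.** Step 2 of the working shows that the direction depends on the marker.
- **Previously infected staff invalidate the cohort.** The lack of an infection-naive criterion is an omission from a condensed article. Sorting subjects by their T0 spike response would also select them on a baseline value of an outcome.

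**Conclusion.** The contradiction holds. The planned T0 precedes or coincides with the day of dose 1, while enrolment is reported as following vaccination, and nothing reconciles the two. How many of the 60 subjects have a true pre-dose baseline cannot be determined from the article. Even if every T0 falls within the stated window, same-day samples may be post-dose, with a distortion of unknown direction that matters mainly for innate markers.

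The multiplicity point holds in a limited form: about 9% false positives per marker for the two contrasts with T0 and about 12% for all three pairs, against a nominal 5%. These figures rest on assumed normal data and exchangeable correlation, and on the tests being run unadjusted, as the flat threshold implies. The article claims no joint error rate for this objective.

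**What to change.** 1. Reconcile the Results sentence with the sampling schedule, stating when the vaccinees were enrolled relative to dose 1.
2. Check the draw time of every T0 sample against the injection time. Restrict the T1-T0 and T2-T0 analyses to subjects whose T0 was drawn before the injection, and report that number.
3. Apply Holm to the T1-T0 and T2-T0 Wilcoxon tests for each marker. If ANOVA is used across the three time points, state that it is the repeated-measures form.

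No new samples are needed, and the article describes the immunological analysis as still ongoing. The cost is a check of dates and times and a few lines of text. The downsides are that the before-after set may be smaller than 60, possibly much smaller, and that Holm sets a somewhat stricter threshold for the first contrast. If few or no pre-dose samples exist, the cohort can still describe cell states after vaccination, but it should not be reported as showing change from baseline.

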## Discussion

According to the medical hypothesis on which the protocol is based, young people could benefit from functional adaptation of innate immune cells induced through epigenetic reprogramming and, especially, pre-existing “partially specific” immunity to community viruses associated with the “bystander effect” of preceding vaccinations [6]. In this study, we will explore the main differences among patients infected by SARS-CoV-2 who experience the illness at different degrees of severity. We will recognize different populations of patients, each one with a specific immunological pattern. There could be differences in terms of cytokines, soluble factor serum levels, and immune cell activity (both of the innate compartment and the acquired one). In this way, the contribution of trained immunity and the bystander effect to protection against SARS-CoV-2 could be explained. Anamnestic data, such as preceding vaccinations and comorbidities, biochemical findings like lymphocyte immunophenotyping, and pre-existing persistent cytomegalovirus infection, allow depicting the risk profile of severe COVID-19. Proof of the roles of these immunological phenomena in the pathogenesis of COVID-19 can be the basis for the implementation of therapeutic immunomodulatory treatments. In addition, the definition of an immunological risk profile could tailor established therapies to each type of patient.

## Abbreviations

ARDS: acute respiratory distress syndrome
BCG: Bacillus Calmette-Guérin
BD: Becton Dickinson
dNK: decidual natural killer
DTP: diphtheria, tetanus, and pertussis
ELISA: enzyme-linked immunosorbent assay
FBS: fetal bovine serum
IFN: interferon
IL: interleukin
LPS: lipopolysaccharide
mAb: monoclonal antibody
NK: natural killer
PBMC: peripheral blood mononuclear cell
PBS: phosphate-buffered saline
RT-PCR: reverse transcription polymerase chain reaction
SMART-COP: systolic blood pressure, multilobar chest radiography involvement, albumin level, respiratory rate, tachycardia, confusion, oxygenation, and arterial pH
Th: T helper
TLR: Toll-like receptor
TNF: tumor necrosis factor
